## Abstract

**Background:**

With demographic change, the number of noncommunicable diseases, chronic diseases and multimorbidity is increasing, and so is the demand for health services. This represents a further challenge for the healthcare system. An adequate and efficient treatment of multimorbid patients requires a well-structured, informed and cross-indicated treatment. Therefore, a new form of coordinated, managed and cross-sectoral care for multimorbid patients - the “MamBo” care model - has been developed. Along with the implementation of MamBo, a process and outcome evaluation will be carried out, which is described in this study protocol. The aim of the study is to evaluate the care model according to its implementation process and effectiveness.

**Methods:**

The MamBo-care model will be evaluated in multi-perspective terms. Thus, a process and outcome evaluation with several data sources will be conducted: (1) Annual focus groups and individual interviews with those involved in the process. (2) Various primary data, including surveys of patients, physicians and practice staff at the time of enrolment and 1 year later to enable pre-post comparison. (3) Claim data from the health insurance of the MamBo population in comparison to a comparative population, formed by the propensity score matching method. (4) Process data of the care management. The analysis of qualitative data will be carried out by content analysis according to Mayring. For the analysis of the quantitative data, multivariate analyses are planned.

**Discussion:**

A new form of coordinated care has been introduced to improve intersectoral care of multimorbid patients and reduce the workload on physicians. The effects of the MamBo care model are being investigated for patients, physicians and the cost units. The results will form the basis for the decision whether the care model should be transferred to standard care and what needs to be taken into account for implementation.

**Trial registration:**

The study was retrospectively registered in the German Register for Clinical Studies (DRKS00014047) on June 28, 2019.

## Background

In the context of demographic change, one of the most important tasks in the future will probably be to guarantee an adequate care for chronically ill and multimorbid patients [1]. As a growing life expectancy is accompanied by increasing life years and multimorbidity, the ageing society is likely to pose further challenges to the health care system [2]. In Germany, the number of people aged 65 and over is rising constantly while every second person at the age of 65 suffers at least from one chronic illness [3]. Multimorbidity is associated with an increased contact with doctors, more frequent and longer hospital stays and an increased number of drug prescriptions (polypharmacy) [4, 5].

The health care of chronically ill and multimorbid patients is very complex, as several physicians and further health as well as social professionals need to be involved in their care. The integration of general medical and specialist care, outpatient, inpatient and nursing care poses a challenge for the health care but in particular for the general practitioners (GP). They are entrusted with the coordination and, thus, they must always be well informed and communicate with all the professionals involved [1]. Adequate and efficient treatment, therefore, requires well -structured, −coordinated and -informed care. However, the highly complex health care system in Germany makes coordinated action more difficult due to its strong segmentation into the outpatient, hospital and nursing care sectors. In addition, there is no overall legal regulation in Germany for gatekeeper strategies. The given structural conditions of primary and secondary care are accompanied by interface problems between the care sectors and between occupational groups in the outpatient sector [6]. The advantages of structured care are proven by the experiences with the Disease Management Programmes (DMP) in Germany [7]. However, DMPs only address isolated disease. There are currently no structures that address the needs of multimorbid patients.

With the Innovation Fund of the Federal Joint Committee of Germany, new models of care that go beyond the regular care are promoted. Every funded study is evaluated under everyday conditions [8]. The findings of the evaluation serve the Federal Joint Committee and the national legislator as a basis for decision-making. The aim is to transfer successful care models to standard health care.

Building upon this, a new form of coordinated, cross-sectoral care for multimorbid patients was developed which is currently being implemented and evaluated. The project supported by the G-BA Innovation Fund is titled: “People with Multimorbidity in Outpatient Care: Patient-Focused and Needs-Oriented Healthcare Management (MamBo)”. MamBo consists of a care management (CM), including responsible persons for the management and up to five monitoring and coordination assistants (MoniKa) set up in a collaborating Regional Health Network (RGL) and a demand management (DM) established on the part of collaborating health insurance. The MoniKas are working on a cross-practice basis and taking over patient-oriented and coordinative tasks (e.g. house calls, patient training, coordination tasks) that can be delegated by doctors. In a continuous improvement process (CIP), the CM and DM, together with the medical practices involved, develop solutions for collective and patients oriented needs (see Fig. 1). An external organisational consulting company supports the initiators of the care model in the implementation.

**Fig. 1 Fig1:**
[figure not shown]
MamBo-structure

The overarching objective of this study is to evaluate the care model MamBo in multi-perspective terms according to its implementation process and effectiveness. This raises the question of which factors seem to be beneficial or inhibiting for the implementation of the innovation and whether the quality and efficiency of care in the region have changed over time. The results will be used in political decision-making to assess whether the model for its transfer to general health care is sufficient, appropriate, economic and necessary.

## Methods/design

### Setting

The new care model MamBo is introduced in a physician’s network in the region of Leverkusen, a small metropolis in North Rhine-Westphalia (Germany). The implementation takes place in established general practitioners or specialist practices. Only physicians who are part of the physicians’ network can participate in MamBo. Currently, it is estimated that approx. 40 physicians and approx. 160 practice staff will participate in the care model. Inturn, approx. 2615 multimorbid patients with at least three chronic diseases and insured with PronovaBKK will be recruited by the participating physicians for the MamBo program. Patients in oncological or palliative treatment are excluded. The initial period of the MamBo-project was set for 3 years (07.2017–06.2020). After applying for an extension of 9 months, due to delays at the start of the study and initial recruitment difficulties, the study now ends on 31 March 2021.

The presented study is a multiperspective evaluation study including a qualitative and a quantitative evaluation design. Qualitative data for process evaluation and quantitative data for outcome evaluation are collected simultaneously. Different domains of the quantitative and qualitative evaluation design are listed in Table 1.

**Table 1 Tab1:** Different domains of the multiperspective evaluation study

Evaluation type	Data source		time of data collection
Process evaluation	focus groups	participating physicians	annual, during the intervention phase
		monitoring and coordination assistants	
	semi- structured interviews	demand management	
		care management	
		management consultancy	once after the implementation
Outcome evaluation	primary data	questionnaire of participating physicians (n ~ 40)	two time-points during the intervention phase
		questionnaire of participating practice staff (n ~ 160)	
		questionnaire of participating patients (t0: n ~ 2460; t0 & t1: n ~ 1500)	
		questionnaire of non-participating physicians within the physician’s network (n ~ 60)	one time-point during the intervention phase
	secondary data	statutory health insurance claim data (group 1: n ~ 1.975; group 2: n ~ 2524)	during and at the end of the intervention phase
		RGL- process data	

### Qualitative evaluation

#### Qualitative evaluation design

Annual focus groups with participating physicians will be conducted to identify factors influencing the implementation and adoption of the innovation. Additionally, the operative actors will be interviewed. In this context focus groups with all employed MoniKas are held each year to gain deep insights into the role of the MoniKas and the complexity of the delegation process. Along with them, annual face-to-face interviews with the DM and the CM will be conducted to discuss the challenges associated with the implementation on a conceptual and organisational level. In addition, one-time expert interviews with representatives of the management consultancy provide deep insights into the complexity, challenges and benefits of change management as an implementation strategy in health care.

#### Sampling

The recruitment of all respondents is conducted purposely [9]. The selection of physicians for the focus groups is based on the Theory Rogers “Diffusion of innovation” [10]. Focus groups with physicians that are active from the beginning (“early adopters”, within the first 6 months) are conducted separately from physicians that become active late (“late adopters”). The board of the RGL provides access to physicians relevant for the respective focus groups. Comprehensively, the research team sends out invitations, information about the procedure and the letters of consent to all participants of face-to-face interviews and focus groups via fax or e-mail.

#### Data collection and analysis

The focus groups and interviews will follow a semi-structured guideline to allow comparisons. For each main topic, open questions are designed. The main topics followed are based on questions regarding inhibiting & facilitating factors of the implementation, expected and perceived advantages, communication and cooperations, work organisation as well as the usefulness of change management for implementation. The guideline will be adopted according to the background and function of the interviewee.

According to process evaluation standards, the interviews are carried out in waves at different times of the projects’ progress. Thus, three focus groups (4–8 physicians each) with participating physicians are planned. One was carried out in June 2018 already and one in January 2019. The second focus group has been supplemented by three individual interviews with doctors in order to gain a deeper insight into the complexity of the implementation and to reach more doctors to share their opinions. If less than four physicians can be recruited for a joint appointment, but other physicians have expressed their interests, additional individual interviews will also be conducted in further data collection waves. The first focus group with MoniKas was carried out in summer 2019, as only at this time an appropriate number of MoniKas with sufficient MamBo-experience (*n* = 3) was available. After a delay in setting up the MamBo-structures, the first interviews with the DM and CM were conducted from May until July 2019. Two management consultants were invited to an interview once in summer 2019.

All interviews will be recorded and transcribed verbatim and pseudonymised [11]. The data will be analysed using qualitative content analysis according to Mayring [12, 13]. For this, the software MAXQDA will be used.

### Quantitative evaluation

#### Quantitative evaluation design

In order to measure effectiveness and treatment effects, postal survey data of all physicians, practice staff as well as patients enrolled in MamBo, will be conducted as a longitudinal study with two time-points. The first questionnaire (t0) is surveyed immediately after the enrolment into the project. The second questionnaire (t1) was originally surveyed 1 year later. As we had difficulties in reaching the required number of patients, the funder proposed to change the intervention period from 1 year to 6 months in the course of the extension application. Due to the fact that the majority of the MoniKa intervention takes place within the first 6 months after enrolment in MamBo and that the MamBo structure is more established in 2020 than in previous years, the evaluation team assumes that a comparison of the groups is still possible and agreed to shorten the period of patient examination. Patients enrolled after November 2019 will, therefore, receive the t1 after 6 months.

Depending on the doctors’ assessment of the patients’ health condition and needs as well as the patients’ wishes, the included patients receive either a MoniKa-home visit, a short MoniKa-call or no MoniKa contact at all. The latter do not receive an additional new form of care and will be considered as the non-treatment group. However, it is expected that they profit indirectly from the MamBo structures on the organisational level. Thus, the patients’ survey can be defined as a cohort study with follow-up and a non-randomized treatment. Non-participating physicians will also be surveyed cross-sectional.

To evaluate the cost-efficiency and effectiveness of the care model secondary claim data will be used. For this, a quasi-experimental cohort study will be conducted. Multimorbid patients (control group) will be compared with multimorbid MamBo-patients (intervention group).

In addition, documentations of the physician network with records of the process-data of the CM provides information about the implementation process.

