### SHI-claim data

#### Sampling

Claim data will be used to assess and compare the costs and use of health services between MamBo patients and patients in standard care. For this purpose, the SHI “PronovaBKK” provides anonymised claim data of the MamBo-population. A statistical twin with data available to the German Health Risk Institute (HRI) [31] is determined for each MamBo participant using the propensity score matching (PSM) method [32]. Matching is performed by the HRI according to criteria such as age, gender and diagnosis.

A sample size of *n* = 2617 corresponding to a statistical power of 79.2% was aimed, given an unpaired t-test, a Cohen’s d of 0.068 and a significance level of 0.05. However, the patients’ enrolment did not correspond to the expected sample size goals, which caused reduced statistical power. To ensure maximum statistical power, the evaluation design of the SHI-claim data analysis has been adopted to the different temporal availabilities of the key parameters. One part can be delivered within 3 months. The other part is available with a delay of up to 9 months. Therefore, group 1 (*n* = 1.975) was closed on 01.04.2019 and group 2 (*n* = 2365) was closed on 01.10.2019. By this, sufficiently high power is guaranteed. The power for Group 1 is about 68% and for Group 2 about 76%.

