#### Data collection and analysis

Both patient-related (e.g. improvements of care,) as well as payer-related (e.g. hospitalizations, utilization of outpatient care) objectives will be considered in the analysis. With MamBo a mean cost reduction of 12,5% is expected due to reduced hospitalization rates. For all variables, a comparison is made between the intervention group and the twin group with significance tests. The selection of the appropriate statistical test depends, among others, on the type (binary/continuous) and distribution of the respective variables.

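### The cost comparison uses insurance claims and no listed source records what MamBo costs to run, so it gives a gross difference that overstates the saving

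*Protocol article*

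**What the plan says.** All places are in the protocol article.

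- **Quantitative evaluation design** assigns the economic question to one source: "To evaluate the cost-efficiency and effectiveness of the care model secondary claim data will be used".
- **SHI-claim data, Sampling** defines the comparison: "Claim data will be used to assess and compare the costs and use of health services between MamBo patients and patients in standard care". Each MamBo participant is matched to a statistical twin.
- **SHI-claim data, Data collection and analysis** gives the expected effect: "With MamBo a mean cost reduction of 12,5% is expected due to reduced hospitalization rates". It does not say whether this is before or after programme cost.
- **Background** lists what MamBo adds to usual care: care management with "up to five monitoring and coordination assistants (MoniKa) set up in a collaborating Regional Health Network (RGL"), "a demand management (DM) established on the part of collaborating health insurance", and a consultancy: "An external organisational consulting company supports the initiators of the care model in the implementation". The project is supported by the G-BA Innovation Fund.
- **Setting, Table 1** and the **Abstract** list the data sources: interviews and focus groups, questionnaires, claims data and RGL process data. None is described as recording programme cost. **RGL process data** covers care management processes and MoniKa activities in aggregate, and its stated purpose is to judge whether implementation succeeded.
- The end of the **Background** says the results will help decide whether the model is "sufficient, appropriate, economic and necessary" for transfer to general care.

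**The concern.** A judgement that a care model is economic has to set what the model costs against what it saves. The source named here measures health-service use and its cost in both groups. The extra staff and structures exist only on the MamBo side. If their cost is not in the claims, every averted admission counts in full while the means of averting it count as nothing. The omission runs in one direction, because the twins have no programme cost to leave out. The result feeds a decision on transfer to standard care, where someone would have to pay for these posts permanently.

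**Working it through.** **1. The plan's own figures.** The stated power concerns the claims difference. Inputs from SHI-claim data, Sampling: d = 0.068, alpha = 0.05, unpaired t-test. With n per group, power = Φ(d·√(n/2) − z).

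| n per group | d·√(n/2) | Power, one-sided (z = 1.645) | Power, two-sided (z = 1.960) | Stated |
|---|---|---|---|---|
| 2617 | 2.460 | 79.2% | 69.1% | 79.2% |
| 1975 (group 1) | 2.137 | 68.9% | 57.0% | about 68% |
| 2365 (group 2) | 2.338 | 75.6% | 64.7% | about 76% |

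The stated values reproduce with a one-sided test. They neither support nor refute this point, but they are needed in step 4.

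**2. What follows without outside figures.** Let c be the running cost per enrolled patient as a percentage of mean claims cost. If the 12.5% is a gross claims reduction, net saving = 12.5% − c. At c = 12.5% or more, the full expected reduction saves nothing.

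**3. Illustrative size.** The article gives neither programme cost nor mean claims cost, so these are assumptions: 50,000 to 70,000 EUR per post per year; 5 posts (MoniKas only) or 8 (adding care and demand management); mean annual claims of 5,000 to 8,000 EUR. The denominator of 2615 patients is from Setting.

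- Expected saving: 0.125 × 5,000 = 625 EUR; 0.125 × 8,000 = 1,000 EUR.
- 5 posts: 5 × 50,000 / 2615 = 96 EUR; 5 × 70,000 / 2615 = 134 EUR per patient-year.
- 8 posts: 8 × 50,000 / 2615 = 153 EUR; 8 × 70,000 / 2615 = 214 EUR per patient-year.
- Share of the saving consumed: 96/1,000 to 134/625, or about 10% to 21%, with 5 posts; 153/1,000 to 214/625, or about 15% to 34%, with 8.
- Break-even claims reduction: from 96/8,000 = 1.2% to 214/5,000 = 4.3% of mean cost.
- Stress case, spreading the cost over group 1 only: 8 × 70,000 / 1975 = 284 EUR, and 284/5,000 = 5.7%.

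Consultancy and set-up cost would come on top.

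**4. Could a significant claims result hide a net loss?** Assume that d = 0.068 corresponds to the 12.5% reduction. Then SD/mean = 0.125/0.068 = 1.84, and the smallest significant reduction is z·√(2/n) × 1.84.

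- Group 1: one-sided 9.6%, two-sided 11.5%.
- Group 2: one-sided 8.8%, two-sided 10.5%.

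All exceed the break-even values in step 3, including the 5.7% stress case. A net loss behind a significant result would need c of about 9% to 10% or more.

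**5. Power for the net difference.** Subtracting a fixed c leaves the SD unchanged, so d scales with (12.5 − c)/12.5. One-sided power, group 1 / group 2: c = 0 gives 69% / 76%; c = 2.5% gives 53% / 59%; c = 5% gives 36% / 40%. A significant gross difference is therefore not in itself evidence of a net saving.

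**The case against.** The strongest reply is that this is a condensed article. Cost components and economic perspective often sit in a fuller evaluation plan, which is not shown and may add programme cost. The article also does not say that claims are the only input to the economic judgement. RGL process data stand beside claims under outcome evaluation in Table 1, and they record the MoniKa activity from which a cost could be built. Describing the claims comparison as one of costs and service use is accurate as far as it goes.

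Part of this stands. How the posts are paid is not stated, so their absence from claims is an inference, though a strong one for network management, insurer staff and a consultancy. What does not stand is that the matter is only missing detail. The article itself assigns cost-efficiency to claims, lists its sources without a programme cost, gives the process data a different purpose, and links the results to an economic judgement.

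A reader might go further and infer that the claims test would present a net loss as a saving, or that the plan calls its result a net saving. The documents support neither. The term net saving does not appear, and on the assumptions above a reduction small enough to be a net loss would not reach significance.

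**Conclusion.** The point holds as one of design and interpretation. As written, the comparison yields a gross difference in payer expenditure, and using it to judge whether MamBo is economic overstates the saving. The true size cannot be derived from the article. On the assumed staffing, salaries and mean claims, with 2615 patients, about 10% to 34% of the expected saving would be consumed, so most of it would survive. A net loss would arise only with a smaller point estimate than the test could declare significant, or with a programme cost well above the assumed range. The conclusion rests on two premises that the article does not state outright: that programme cost is not in the patient-level claims, and that the 12.5% is meant before programme cost.

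**What to change.** 1. Label the claims difference as a gross difference in payer expenditure wherever it is reported.
2. Report as the economic result a net difference: claims cost plus running programme cost per enrolled MamBo patient (care management, MoniKas, demand management), minus claims cost of the twins. Average the cost over all enrolled patients, including those without MoniKa contact, because all of them are in the comparison.
3. Show set-up and consultancy cost separately, since they may not recur in standard care.
4. Take costs from project accounts and quantities from the RGL activity records. Aggregate records are enough for a mean cost per patient. Vary that cost over a plausible range.
5. If part of the programme cost does turn out to be in the claims, say which part and do not count it twice.

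No new patient data are needed and the matching is unchanged. The cost is a modest costing exercise, assuming that the partners can supply the accounts, and a less favourable stated saving. If the accounts cannot be had, step 1 alone still prevents the misreading, but the report should then draw no conclusion on whether the model is economic.
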